### Other measures

Participant demographic data (sex, age, occupation and time spent barefoot per day) and body size (height and body mass) will be obtained at baseline for the description of the population.

### Sample size

Due to the exploratory nature of this novel research with the use of MRI and within funding constraints, a sample size of 20 participants (10 per group) will be enrolled into this feasibility study. Sample sizes of this magnitude will best provide estimate parameters for determining a clinical trial that seeks to identify large standardised effect sizes [50].

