Three studies have evaluated interventions for PHP that have included IFM training [17–19]. Two of these studies [18, 19] have investigated 4 weeks of multimodal interventions where IFM exercise was combined with manual therapy, electrotherapy, stretching and/or medication. In these studies, as IFM exercise was a component of a combined package of interventions, and was included in the intervention for both comparator groups, the effect of IFM training is difficult to determine. The other study [17] investigated the addition of IFM exercise to calf stretching over 8 weeks and reported no difference when compared to calf stretching alone. In that study, there were several limitations that may have influenced the effectiveness of the IFM exercise programme. For example, there were only two exercises that targeted the IFMs (toe curl exercise and short foot exercise) that were performed under supervision of a physiotherapist for 8 weeks (16 sessions in total). The toe curl exercises were performed for 3 sets of 15 repetitions with graduated resistance of 1 and 2 kg weights and the short foot exercise for 3 one-minute isometric holds in single limb stance. The exercise programme was likely insufficient for hypertrophy/strength gains [20], but it remains unknown, as there was no measurement of IFM structure and/or strength. Two other studies in healthy populations, have reported increased IFM size (10–21%) and strength (35–106%) with a programme that involved more than two foot exercises, at higher intensities and larger volumes [21, 22]. IFM training with sufficient volume, intensity and progression may produce more beneficial results in PHP compared to previous trials.

The primary aim of this study is to investigate the feasibility of conducting a full-scale randomised clinical trial (RCT), as well as the credibility and acceptability of a foot exercise plus education intervention in individuals with PHP. The secondary aim is to investigate treatment response (effect sizes) using a comprehensive set of measurements which consists of pain, physical function, physical activity level, pain self-efficacy, perceived treatment effect, MRI and ultrasound image measurement of IFM morphology, ultrasound imaging measurement of plantar fascia thickness, IFM motor performance, foot posture, foot mobility, ankle dorsiflexion range of motion, toe flexor and plantar flexor strength/endurance.

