## Methods

### Design

This protocol describes a feasibility study of a prospective, assessor-blinded, randomised clinical trial with two parallel groups and a 12-week intervention period (Fig. 1). Participants will be randomised to each group using a 1:1 ratio (see ‘Allocation’ for more detail regarding randomisation). The primary end point is 12 weeks. The trial will be conducted in physiotherapy clinics in Brisbane, Australia and The University of Queensland. This study protocol follows the Standard Protocol Items: Recommendations for Interventional Trials (SPIRIT) guidelines [23]. The trial was prospectively registered with the Australia and New Zealand Clinical Trial Registry on 11th July 2019 (ACTRN12619000987167; http://www.ANZCTR.org.au/ACTRN12619000987167.aspx).

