### Statistical analysis

Data will be analysed on an intention-to-treat basis. Primary outcomes will be presented as descriptive statistics. To explore treatment effects *(secondary aim)*, descriptive data (group means, standard deviation) and mean differences (95% confidence intervals) for within and between-group comparisons will be reported. To provide an indication of the magnitude of observed differences, standardised mean differences (mean difference / pooled standard deviation) will also be calculated. Changes within and between groups will be considered in relation to reported scores of meaningful change and measurement error. The descriptive data and point estimates of treatment effects reported from this study will be used to calculate the required sample size for a full-scale RCT.

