## Discussion

PHP is a recurrent and persistent musculoskeletal condition that affects a wide range of individuals. The burden of the condition is significant with low physical activity levels, poor quality of life and higher rates of stress, anxiety and depression [2, 9]. Current evidence to guide selection of treatment options for PHP is limited, with several systematic reviews reporting that treatment effects are small, ineffective when compared to placebo or of short duration only (1–6 weeks) [51–54]. In terms of IFM exercise for PHP, only three superiority trials have been conducted and results provide little evidence to guide the use of exercise for PHP.

Our feasibility study of a prospective assessor-blinded randomised clinical trial will be the first to evaluate the feasibility of a full-scale RCT, as well as treatment response, of a progressive foot focused exercise plus education intervention for the management of PHP, when compared to a wait and see approach (brief advice). The FEET trial will address several limitations of previous investigations, such as exercise programmes with insufficient training volume and intensity, number of exercises, lack of progression and integration to functional positions. The exercise program in this study was developed based on existing biomechanical studies that have reported the function of the IFMs during walking and running [11–13]. Accordingly, the exercises are designed to train the foot for these functional requirements. For example, our program will incorporate varied contraction types (i.e. isometric, concentric and eccentric); functional weight bearing positions; progressive loading via seated, two-leg or single-leg weight bearing or increasing resistance tubing; incorporation of functional tasks (e.g. calf raise to mimic propulsion and squat to mimic stance phase absorption) and rate of loading (e.g. jumping and hopping). The exercise program has been refined through pilot investigations and feedback from individuals with PHP and physiotherapists practicing in the Brisbane region. A novel feature of the FEET trial is the inclusion of a comprehensive set of physical measurements (including IFM morphology), which will help to explore potential mechanisms of effect, whereas existing investigations have focused solely on patient-reported outcomes. An improved understanding of potential mechanisms of effect is a preliminary step towards identifying individuals that may be more suited to this approach.

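### The main trial is to be sized on the pilot's point estimates of treatment effect, which 10 participants per group cannot estimate well enough for that use

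*Protocol article*

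**What the plan says.** All references are to the protocol article.

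- **Sample size** gives a practical ground first: the work is exploratory, uses MRI and is limited by funding. On that basis, "a sample size of 20 participants (10 per group) will be enrolled into this feasibility study". The one statistical ground follows: "Sample sizes of this magnitude will best provide estimate parameters for determining a clinical trial that seeks to identify large standardised effect sizes". No numerical target effect is given.
- **Statistical analysis** plans group means, standard deviations (SDs) and mean differences with 95% confidence intervals, and adds that "standardised mean differences (mean difference / pooled standard deviation) will also be calculated". It then fixes the use of the results: together with the descriptive data, the "point estimates of treatment effects reported from this study will be used to calculate the required sample size for a full-scale RCT". The end of the Discussion repeats that the results will feed the sample size of the full-scale trial.
- **Background and Discussion** review the evidence. The Discussion cites "several systematic reviews reporting that treatment effects are small, ineffective when compared to placebo", or short-lived. In the Background, the one trial that added intrinsic foot muscle exercise to calf stretching "reported no difference when compared to calf stretching alone".
- **Secondary outcome measures** cites meaningful-change scores: 2 points on the pain scale, and 8 and 9 points on the two Foot and Ankle Ability Measure subscales.

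**The concern.** Two statements combine badly. Sample size says that about 10 per group suits planning a main trial that looks for a large standardised effect. Statistical analysis says the observed effect will help set the size of that trial. Read together, they imply that the pilot's effect estimate is good enough to plan on.

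A required sample size varies with one over the square of the effect, so error in a small pilot's estimate is magnified. A pilot that overstates the effect by chance leads to an underpowered main trial. One that shows nothing, or a difference in the wrong direction, gives no usable sample size at all. The article also offers no direct evidence that a large between-group effect on pain or function is to be expected.

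**Working it through.** **Inputs.** From the article: 10 per group (Sample size), 1:1 allocation (Design), SMD = mean difference / pooled SD (Statistical analysis). Assumed, because the article does not state them: two-sided 5% level, 90% power for the main trial, normal outcomes with equal SDs, no drop-out, and large meaning an SMD of 0.8. The article gives no power calculation, so there is no figure of its own to reproduce.

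**1. Precision of the effect estimate.** Degrees of freedom are 10 + 10 - 2 = 18.
- Half-width of the 95% interval for a mean difference: 2.101 × √(2/10) = 0.94 SD.
- Interval for an SMD: t = d × √(10/2) = 2.236d. Find the noncentrality values that place t at the 97.5th and 2.5th percentiles, then divide by 2.236.

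| Observed SMD | t | Noncentrality limits | 95% CI for SMD |
|---|---|---|---|
| 0.5 | 1.118 | -0.890, 3.096 | -0.40 to 1.38 |
| 0.8 | 1.789 | -0.278, 3.810 | -0.12 to 1.70 |

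**2. Main-trial size needed.** Normal approximation per group: n = 2(1.960 + 1.282)²/d² = 21.01/d².
- d = 0.3: 233.5, so 234
- d = 0.5: 84.1, so 85
- d = 0.8: 32.8, so 33

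The t-based values are one larger in each case.

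**3. Sizing on the point estimate.** Because n varies with 1/d², the planned n falls below half the needed n when the observed SMD exceeds √2 times the true SMD. The chance of that is the upper tail of a noncentral t on 18 degrees of freedom with noncentrality 2.236d, beyond √2 × 2.236d.

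| True SMD | Noncentrality | Cut-off | Less than half the needed n | Observed SMD of 0 or less |
|---|---|---|---|---|
| 0.3 | 0.671 | 0.949 | 40% | 25% |
| 0.5 | 1.118 | 1.581 | 33% | 13% |
| 0.8 | 1.789 | 2.530 | 26% | 4% |

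Simulation with 200,000 pilots and n rounded up gave 40%, 33% and 25%, so rounding moves only the last figure. At exactly half the needed n, power is about Φ(3.242/√2 - 1.960) = Φ(0.33) = 63% instead of 90%; below half it is lower still.

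**4. What the pilot can say about the SD.** Chi-square limits on 18 degrees of freedom:
- 95% limits: √(18/31.53) = 0.76 to √(18/8.23) = 1.48 times the estimate, hence 0.57 to 2.19 times the plug-in n.
- One-sided 80% upper limit: √(18/12.86) = 1.18 times the SD, hence n × 1.40.

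The SD is loosely known, but a stated margin can cover that.

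**5. The alternative for the pain scale.** Target difference 2 points (cited in the article). The article gives no SD, so 2 to 3 points is assumed. Per group, n = 21.01 × SD²/2².
- SD 2: 21.0, so 22; × 1.40 = 29.4, so 30.
- SD 3: 47.3, so 48; × 1.40 = 66.2, so 67.

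The result depends on one estimated quantity with a stated margin, and not on the observed effect.

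**The case against.** A reader might go further and infer any of four things. The case against each is good.

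- **That 10 per group is justified only by a large effect.** It is not. Exploratory work, MRI and funding come first, and that is an accepted basis for a feasibility study whose primary outcomes are descriptive.
- **That the article contradicts itself on effect size.** It does not. The small effects in the Discussion concern other treatments. The Background explains the null trial as probably under-dosed, and its comparator was calf stretching, whereas here it is deliberately minimal advice. The Background also cites sizeable gains in muscle size (10–21%) and strength (35–106%) in healthy people. Those gains are not evidence on pain or function, so the premise remains unsupported there and in tension with the review.
- **That the pilot cannot supply planning parameters.** It can give feasibility data and a rough SD. If only the SD is taken from the pilot, the pilot size that minimises pilot plus main-trial numbers at 90% power is 7 to 10 per group for an SMD of 0.8, 10 to 16 for 0.5, 17 to 25 for 0.3 and 27 to 44 for 0.2, depending on the inflation method. Ten is adequate for a large effect, borderline for a moderate one and low for small ones.
- **That precision for the feasibility proportions is wrongly absent.** A condensed article may leave that to the full protocol.

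The article also does not say that the main trial will assume a large effect, or that a null estimate would end the programme. It does plan confidence intervals and a comparison with meaningful-change scores, but for interpreting results and not as the sample-size input. The planning rule itself has no answer: it is stated outright, and the imprecision holds even when the true effect is large.

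**Conclusion.** The concern holds for the planning rule in Statistical analysis, and for the large-effect sentence in Sample size so far as it lends that rule support. With 10 per group, even an observed SMD of 0.8 is compatible with values from slightly below zero to 1.70. Planning on the estimate would more than halve the needed sample in roughly a quarter to two fifths of pilots over true SMDs of 0.3 to 0.8. Drop-out would make this worse: with 8 analysed per group, the interval half-width grows from 0.94 to 1.07 SD.

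The large-effect premise aggravates the problem but does not cause it. The figures rest on the assumed 5% two-sided level, 90% power and normal outcomes. The √2 threshold does not depend on the level or power chosen, so the percentages in step 3 hold for other choices too, apart from rounding. The enrolled number is not at fault. This should be changed before the main trial is sized.

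**What to change.** - **Statistical analysis:** remove the point estimates of treatment effect as a sample-size input. State that the main trial's target difference will come from the meaningful-change scores already cited (2 points on the pain scale; 8 points for activities of daily living and 9 for sports on the Foot and Ankle Ability Measure). Take only the SD from the pilot, at a conservative upper confidence limit. The one-sided 80% limit (1.18 × SD, n × 1.40) is one reasonable convention; another may be chosen if stated in advance.
- **Sample size:** keep the practical rationale. Qualify the large-effect sentence so that it does not imply that the pilot's effect estimate is adequate for planning.
- **Cost:** wording only, with no extra participants here. The stated rationale becomes less favourable, and the planned main trial may be larger. Trial status records that follow-up ended on 31 January 2020, so the change belongs in the results report and the main-trial design.

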### Statistical analysis

Data will be analysed on an intention-to-treat basis. Primary outcomes will be presented as descriptive statistics. To explore treatment effects *(secondary aim)*, descriptive data (group means, standard deviation) and mean differences (95% confidence intervals) for within and between-group comparisons will be reported. To provide an indication of the magnitude of observed differences, standardised mean differences (mean difference / pooled standard deviation) will also be calculated. Changes within and between groups will be considered in relation to reported scores of meaningful change and measurement error. The descriptive data and point estimates of treatment effects reported from this study will be used to calculate the required sample size for a full-scale RCT.

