#### Inclusion criteria

Volunteers will be included if they satisfy the following criteria.
Over 18 years of age.Report a history of insidious onset pain under the sole of the foot, located at the heel, that has persisted for more than 3 months.Report pain that is most noticeable with initial steps following a period of inactivity, and also worsened with prolonged weight bearing [1].Report worst first step pain during the previous week of greater than 3/10 on a numerical rating scale (0 = no pain; 10 = worse pain imaginable).Report pain on palpation of the medial calcaneal tubercle or proximal fascia.Plantar fascia thickness is 4 mm or greater when measured using ultrasound imaging.

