### Allocation

Following baseline assessment, participants will be randomised via concealed allocation to either foot exercise and education or wait and see (brief advice). A computer generated randomization schedule will be used, allocating on a 1:1 ratio in random permuted blocks of 2–6 [24]. A study investigator (RM) who is not involved in recruitment or outcome assessment will manage the randomisation allocation and liaise with the treating physiotherapist regarding group allocation. As treating physiotherapy clinics are located in various suburbs of Brisbane, participants may select the most convenient practice for them to attend. Participants will be informed of group allocation by the treating physiotherapist.

The interventions will be delivered by registered physiotherapists, who regularly treat musculoskeletal conditions, in seven private practices across Brisbane. To ensure consistent implementation of both interventions, treating physiotherapists will attend 2 training sessions of 90-min duration each, 1 week apart, at The University of Queensland prior to commencement of the trial. Trial physiotherapists will also be provided with a trial handbook (detailed documentation including images, instructions and progressions of exercises) and advised to contact the study investigators for any queries that arise during the trial.

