### Outcome measures

To ensure sufficient information is obtained to inform the design of a full-scale RCT, a comprehensive set of primary and secondary outcome measures will be recorded (Table 2). Outcome measures will be assessed at baseline and 12-week time-points (at the end of the intervention period). The 12-week time period for measuring outcomes allows an adequate timeframe to observe adaptations, allowing for (a) a 2-week lead in period of familiarisation and movement competency training, (b) an 8-week strengthening programme, (c) graduated progression of exercise, and (d) integration into functional tasks. All outcome measures will be obtained by an assessor who is blinded to group allocation ([name]).

**Table 2 Tab2:** Outcome measurements

		STUDY PERIOD		
		Enrolment/ Baseline	Post-allocation	Close-out
**TIMEPOINT**^**a**^		**t**_**0**_	**t**_**1**_	**t**_**2**_

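### The between-group effect on secondary outcomes is stated without baseline adjustment, although all but one have a baseline value; with 10 per arm this gives up precision and leaves chance imbalance in the estimate

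*Protocol article*

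**What the plan says.** The Statistical analysis section states that "descriptive data (group means, standard deviation) and mean differences (95% confidence intervals) for within and between-group comparisons will be reported". It then defines the standardised difference as the mean difference over a pooled SD, without saying whether that is the baseline, 12-week or change SD. It names no covariate, and no other section does. It also does not settle whether the between-group difference is taken on 12-week values or on changes. A later sentence, which sets changes against published thresholds for meaningful change and measurement error, hints at changes. The section ends by feeding the effect estimates into the sample size of the full-scale trial.

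On the data available, the Outcome measures section says: "Outcome measures will be assessed at baseline and 12-week time-points". In Table 2 every secondary outcome is marked at both times except the global rating of change, which is marked only at week 12. The Sample size section says that "a sample size of 20 participants (10 per group) will be enrolled into this feasibility study". The Allocation section describes "allocating on a 1:1 ratio in random permuted blocks of 2–6" and mentions no stratification on a baseline outcome.

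**The concern.** With 10 per arm, randomisation often leaves visible differences in baseline pain, function or muscle size. Neither unadjusted estimator handles them fully. A difference in 12-week values keeps the part of the imbalance that persists to follow-up, and a difference in changes over-corrects for it. Regressing the 12-week value on arm and baseline value removes the shift in expectation, and usually narrows the interval as well. The data for it are already in the design.

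Estimating treatment response is the stated secondary aim, and the resulting estimates are meant to size the next trial. What is at stake is how noisy those planning figures are, and whether the report yields the residual SD and correlation that an efficient full-trial design would use.

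**Working it through.** There is no figure in the plan to reproduce: the 20 participants were set on pragmatic grounds, without a power calculation. The check therefore compares the three possible estimators at that size.

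**Inputs.** From the article: n = 10 per arm, 1:1 allocation, one baseline and one 12-week value per outcome. Assumed: r, varied from 0 to 0.95; equal SDs at the two times; a linear relation with a common slope; all 20 participants measured.

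**Chance imbalance.** The SE of the baseline difference is sqrt(2/10) = 0.447 SD. The probability that it exceeds 0.5 SD in either direction is 2 × (1 − Φ(0.5/0.447)) = 0.26 for any one outcome.

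**Effect of a 0.5 SD imbalance.** It shifts the 12-week difference by 0.5 × r and the change difference by 0.5 × (r − 1). At r = 0.5 these are +0.25 and −0.25 SD. At r = 0.7 they are +0.35 and −0.15 SD. The expected shift with ANCOVA is zero.

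**95% CI half-width, in outcome SDs.**
- 12-week values: t(18) × sqrt(0.2)
- Changes: t(18) × sqrt(0.2 × 2(1 − r))
- ANCOVA: t(17) × sqrt(0.2 × (1 − r²) × (1 + 1/16)), where 1/16 is the average cost of estimating the slope

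| r | 12-week | Change | ANCOVA | ANCOVA / 12-week | ANCOVA / change |
|---|---|---|---|---|---|
| 0 | 0.940 | 1.329 | 0.973 | 1.035 | 0.732 |
| 0.3 | 0.940 | 1.112 | 0.928 | 0.987 | 0.835 |
| 0.5 | 0.940 | 0.940 | 0.842 | 0.896 | 0.896 |
| 0.7 | 0.940 | 0.728 | 0.695 | 0.739 | 0.954 |
| 0.9 | 0.940 | 0.420 | 0.424 | 0.451 | 1.009 |
| 0.95 | 0.940 | 0.297 | 0.304 | 0.323 | 1.022 |

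ANCOVA breaks even with 12-week values at r of about 0.26 and with changes at about 0.87.

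**Simulation check.** With 20,000 simulated trials at r = 0.5, mean half-widths were 0.93, 0.93 and 0.83, and coverage was about 95% for all three estimators.

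**Relevance to the full trial.** For an illustrative effect of 0.5 SD at 80% power and two-sided 5%, n per arm is about 2 × (1.96 + 0.84)² / 0.5² = 63 on 12-week values. The multiplier is 2(1 − r) for changes and 1 − r² for ANCOVA. At r = 0.5 this gives 63 for changes and 48 for ANCOVA; at r = 0.7 it gives 38 and 33. These savings can be planned only if r and the residual SD are reported.

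**The case against.** The strongest reply is that the section never says unadjusted. An ANCOVA coefficient is also a mean difference with a 95% CI, and model form is often left to an analysis plan that is not shown here. That stands as a limit: the absence of adjustment is inferred from an estimator stated in full with no covariate. It does not dispose of the point, because the article does fix the estimator, including its standardised form as mean difference over pooled SD, and nothing shown points to adjustment.

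A reader might go further and infer that the planned estimates are biased or the intervals invalid. The documents do not support that. Over repeated randomisation both unadjusted differences are unbiased, and their intervals hold their coverage. The imbalance shift is part of the sampling error that those intervals already express. These are also exploratory secondary outcomes, with no hypothesis test resting on them.

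The size of the gain is also uncertain. If change scores are intended, the gain is small at r = 0.7 and gone by about 0.87. High values are plausible for stable physical measures: the article cites test-retest ICCs of 0.96 to 0.99 for heel rise, foot posture and the lunge test, although these are not 12-week correlations. Nor does adjustment make 20 participants a firm basis for an effect size: a half-width of 0.84 SD is still wide.

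A reader might also infer that within-group improvement will be taken as evidence of efficacy, since entry requires a minimum pain score ("Report worst first step pain during the previous week of greater than 3/10 on a numerical rating scale") and symptoms can resolve untreated. The article does not say so. It reports within-group change beside a randomised comparison with a wait-and-see arm, and such description can stay.

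**Conclusion.** The point holds as a worthwhile improvement, not as an error. As stated, the between-group estimate makes no use of the baseline values collected for every secondary outcome but one. The 26% chance of an imbalance above 0.5 SD per outcome follows from 10 per arm alone. The precision gain rests on an assumed r. It is about 10% over either alternative at r = 0.5; at r = 0.7 it is 26% over 12-week values and 5% over changes. The possible loss is small: up to 3.5% against 12-week values when r is below about 0.26, and about 2% against changes at r = 0.95, the highest value tried. The global rating of change is unaffected. The primary feasibility, credibility and acceptability outcomes, which are purely descriptive, are not touched.

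**What to change.** For each secondary outcome with a baseline value, report the between-group effect as the adjusted mean difference (95% CI) from a linear model of the 12-week value on arm and baseline value. Leave the global rating of change unadjusted. Report the residual SD and the baseline-to-12-week correlation for each outcome, so that the full trial can be sized for the analysis it will use.

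State which SD forms the denominator of the standardised difference. The pooled baseline SD is not an automatic choice: the entry thresholds on first-step pain and fascia thickness may narrow the baseline spread of those measures and so inflate the standardised effect. Within-group changes may remain as description.

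The cost is a short addition to the analysis section and one degree of freedom per model, with no new data. The Trial status section puts the last follow-up measurement at 31 January 2020, before publication, so the adjusted analysis should be labelled as specified after data collection.

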A LOGIQ V2 ultrasound machine (GE Healthcare, Illinois, USA) equipped with a linear array probe (6-12 MHz) will be used to obtain images of the IFMs. Cross-sectional area of the abductor hallucis and thickness of the muscles of the first interstitial space (adductor hallucis, first dorsal interossei and first lumbrical) will be imaged in sitting and standing positions using previously established methods [37]. For abductor hallucis, cross-sectional area will be measured from transverse images obtained on a scanning line drawn in an inferior direction from the most anterior aspect of the medial malleolus. Thickness of the muscles of the first interstitial space will be measured from longitudinal images obtained on a scanning line between the first and second metatarsal bones. Cross-sectional area of flexor digitorum brevis, quadratus plantae and flexor hallucis brevis will be measured from transverse images obtained with the participant in prone with the foot relaxed over the edge of the bed [38]. The thickest portion of the flexor digitorum brevis and quadratus plantae muscles will be located in longitudinal along a scanning line from the medial tubercle of the calcaneus to the third toe, and then the probe rotated to 90 degrees to measure the cross-sectional area. For flexor hallucis brevis the thickest portion of the muscle will be located in longitudinal along the first metatarsal shaft and then the probe rotated to 90 degrees to measure the cross-sectional area. For reproducibility at follow-up, the location of the probe will be recorded as the linear distance from the posterior aspect of the calcaneus. Ultrasound images will be stored and measured offline using medical imaging software (Osirix MD, Pixmeo SARL, Geneva, Switzerland). Test-retest reliability of these measures is high with ICCs 0.81 to 0.98, standard error of measurement (SEM) 0.13 to 0.17cm for thickness and 0.13 to 0.19cm^2^ for cross-sectional area, and minimal detectable change (MDC) of 0.36 to 0.48cm for thickness and 0.14 to 0.53cm^2^ for cross-sectional area [37, 38].

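### The between-group contrast is left undefined (12-week values or change) and no baseline-adjusted estimate is named, although baselines are collected and the point estimates feed the full-scale sample size

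*Protocol article*

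**What the plan says.** For the secondary aim, the Statistical analysis section of the protocol article promises group means and SDs, and states that "mean differences (95% confidence intervals) for within and between-group comparisons will be reported". It adds that "standardised mean differences (mean difference / pooled standard deviation) will also be calculated". No regression model or covariate is named. The next sentence reads "Changes within and between groups will be considered in relation to reported scores of meaningful change and measurement error", which hints at change scores but does not define the between-group contrast. The section ends by sending the descriptive data and the point estimates into the sample size calculation for a full-scale RCT.

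Under Outcome measures, "Outcome measures will be assessed at baseline and 12-week time-points". Table 2 shows both time points for every secondary outcome except global rating of change, which is taken at 12 weeks only. The Sample size section states that "a sample size of 20 participants (10 per group) will be enrolled into this feasibility study". The Allocation section describes "allocating on a 1:1 ratio in random permuted blocks of 2–6" and mentions no stratification.

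**The concern.** With 20 participants and no stratification, the arms can easily differ at baseline by chance. A difference in 12-week means carries r times that imbalance. A difference in mean change carries (r - 1) times it, so it errs in the opposite direction. Which of the two is reported therefore matters, and the text does not settle it. A baseline-adjusted difference removes this component in expectation, and the data for it are already being collected.

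The stakes lie in how the results will be used. The estimates are exploratory, but the plan takes their point values forward to size the next trial. If that trial is analysed with baseline adjustment, its sample size also depends on r and on the residual SD, and the plan does not list either among the quantities to be reported.

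**Working it through.** The protocol gives no alpha, power, effect size or SD for its 20 participants, so there is no figure of its own to reproduce.

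**Inputs.** n = 10 per arm (Sample size section). Equal SDs at both time points, set to 1, and no dropout are assumptions. The correlation r between baseline and 12 weeks is not in the document, so it is varied.

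**1. Chance imbalance.** The SE of the baseline difference is sqrt(2/10) = 0.447 SD.
- P(|difference| > 0.3 SD) = 2[1 - Φ(0.3/0.447)] = 50%
- P(|difference| > 0.5 SD) = 2[1 - Φ(0.5/0.447)] = 26%

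**2. Shift caused by a 0.5 SD imbalance.** The 12-week contrast shifts by 0.5r and the change contrast by 0.5(r - 1).
- r = 0.5: +0.25 SD and -0.25 SD
- r = 0.7: +0.35 SD and -0.15 SD

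**3. Expected 95% CI half-width, in SD units.**
- 12-week values: t18 × 0.447 = 0.94
- change: t18 × 0.447 × sqrt(2(1 - r))
- ANCOVA: t17 × 0.447 × sqrt(1 - r²) × sqrt(17/16), where 17/16 is the average price of estimating the slope with 20 people

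| r | 12-week | change | ANCOVA | ANCOVA v 12-week | ANCOVA v change |
|---|---|---|---|---|---|
| 0.1 | 0.94 | 1.26 | 0.97 | 3% wider | 23% shorter |
| 0.3 | 0.94 | 1.11 | 0.93 | 1% shorter | 17% shorter |
| 0.5 | 0.94 | 0.94 | 0.84 | 10% shorter | 10% shorter |
| 0.7 | 0.94 | 0.73 | 0.70 | 26% shorter | 5% shorter |
| 0.9 | 0.94 | 0.42 | 0.42 | 55% shorter | 1% wider |

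A simulation of 20,000 trials at each of these five values gave the same ordering. Setting the half-widths equal gives break-even points of r = 0.26 against 12-week values and r = 0.87 against change.

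**4. What the shift could do to the next trial (illustration).** Assume a true standardised effect of 0.8, two-sided 5% and 80% power. Then n per arm = 2(1.960 + 0.842)²/d² = 15.70/d².
- d = 0.80: 24.5, so 25
- d = 0.80 + 0.25 = 1.05: 14.2, so 15
- d = 0.80 - 0.25 = 0.55: 51.9, so 52

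At r = 0.5 the SD of change is sqrt(2(1 - 0.5)) = 1, so both contrasts are on the same scale. The same imbalance, read through the two contrasts that the text allows, gives 15 or 52 per arm.

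**The case against.** The strongest reply is that silence is not a decision. The article never calls the differences raw or unadjusted, an adjusted difference is also reported as a mean difference with a 95% CI, and covariates may be set in an analysis plan that is not shown. This stands. A reader might infer that the plan commits to unadjusted 12-week comparisons, and the text does not support that. What it does show is an estimator described without a covariate and a contrast left undefined.

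Second, the mention of changes, and the published thresholds quoted for many outcomes, point towards change scores, which do use the baseline. This also stands in part. For a highly correlated measure a change score loses almost nothing to ANCOVA. It would be tempting to take the muscle ultrasound statement, "Test-retest reliability of these measures is high with ICCs 0.81 to 0.98", as evidence of high r and to argue that 12-week differences in muscle size would mostly reflect who was allocated where. Those figures describe repeatability, not correlation across 12 weeks of treatment, and the argument falls away if change is the contrast.

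Third, both unadjusted contrasts are unbiased over randomisation. This is correct: the shift is conditional on the allocation that occurs, so the planned analysis is not biased in general. Nor can one say without qualification that its intervals are wider than the data allow, because that fails outside the break-even points.

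Fourth, r can be recovered. A paired within-group CI yields the SD of change, and r = (SD0² + SD1² - SDchange²)/(2 × SD0 × SD1). This is right, so r is not lost. Reporting it directly is simply better.

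Finally, effects are a secondary, exploratory aim, and an adjusted half-width of 0.84 SD at r = 0.5 is still very wide. Adjustment does not make a 10-per-arm point estimate a secure basis for a sample size. That limits the weight of the point without removing it.

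**Conclusion.** The point holds in limited form and is worth acting on. The Statistical analysis section does not define the between-group contrast and names no baseline-adjusted estimate, although baselines exist for every secondary outcome but one. An imbalance above 0.5 SD has a probability of about 26%. At an assumed r = 0.5, a 0.5 SD imbalance moves the two candidate contrasts by 0.25 SD in opposite directions, conditional on the allocation.

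The precision gain depends on r, which the protocol does not give. It is about 10% at r = 0.5 against either contrast, and 26% (12-week values) or 5% (change) at r = 0.7. There is none below about 0.26 against 12-week values or above about 0.87 against change, where the loss is only about 1-3%. ANCOVA is therefore the safer default when r is unknown: it is never much worse than either contrast, whereas each of them is clearly worse over part of the range. These figures assume equal SDs, full follow-up and approximately normal outcomes.

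**What to change.** State in the Statistical analysis section that, for each continuous or approximately continuous secondary outcome with a baseline value, the between-group difference at 12 weeks will be estimated by linear regression on arm and baseline value (ANCOVA), with its 95% CI. Report the baseline to 12-week correlation and the residual SD beside the group means and SDs, and use them in the full-scale sample size calculation. For a baseline-adjusted trial the required number scales with 1 - r², for example 1 - 0.25 = 0.75 of the unadjusted number at r = 0.5. Within-group changes can still be set against the published thresholds as planned.

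Global rating of change has no baseline and needs no adjustment. The 0-3 ordinal motor performance ratings need not be forced into a linear model with 20 people.

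The cost is a sentence or two of text and one degree of freedom per model (17 instead of 18 with complete data). No new data are needed.
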